### Intervention

The intervention that will be investigated is called Mindlight. This is a video game aimed at children of 8–16 years old and is based on principles of cognitive-behavioural therapy (CBT) and neurofeedback, which are evidence-based interventions for anxiety-disordered children and adults. Briefly, the premise of the game is that Little Arthur is left on the doorstep of a scary mansion by his parents. Arthur must learn to use his own inner strength to overcome his greatest fears so the shadows in the house can hold no power over him. He can accomplish this by using his Mindlight, a light bubble that can shine on the surroundings and that can be controlled by his own inner strength. This ‘inner strength’ will be measured by a neurofeedback headset (the ‘MindWave’; Neurosky USA; [33]), which children will put on when they are going to play Mindlight. This headset records EEG using dry sensor technology, which consists of an active and reference electrode. The signals that are measured will be filtered on Delta, Theta, Alpha and Beta waves. In Mindlight, especially the Alpha and Beta waves will be used for real time feedback. Research has shown that the Mindwave headset has good reliability and validity [33], and that it can be used in research with children who have a developmental disorder (*e.g.* ADHD; [34]).

In Mindlight, the Alpha and Beta waves will be used in several ways. First of all, the recorded Alpha waves reflect the degree of relaxation of the child. This feature is used in the exposure techniques (CBT) that are embedded in the game (see also Fig. 2): when the child sees threatening stimuli (*e.g.* monsters) several times during the game and learns to maintain calm when facing them, the child eventually gets habituated to them and can gain points more easily.

**Fig. 2 Fig2:**
[figure not shown]
Relaxation mechanic Mindlight: remain calm to enlighten environment

Furthermore, the recorded Beta waves reflect the degree of concentration and the allocation of attention of the player. Focused concentration allows the player to solve attention bias modification (ABM) puzzles. ABM is a training protocol that has its roots in CBT and that is based on the idea that distorted cognitions, particularly attentional biases characterized by hyper attention towards potential threats, play a role in the pathogenesis of childhood anxiety [22]. ABM has been shown to reliably reduce anxiety by retraining the attentional system to focus on positive stimuli [35]. Mindlight uses this principle in the ABM-puzzles, by rewarding children for focusing on positive aspects of the environment (measured by the neurofeedback device). More specifically, they learn to move towards, and quickly respond to, positive stimuli (*e.g.*, portraits of happy faces) and disattend to, or shift attention away from, negative stimuli (*e.g.*, mean faces, threatening animals).

To minimize the chance of finding placebo-effects of Mindlight, children in the control condition will also receive a computer game. In this way, the amount of attention that children in the experimental condition and children in the control condition receive is equal, and the effects that may be found can uniquely be ascribed to the game itself. The computer game that the children in the control condition are going to play is called ‘Triple Town’. In this puzzle game, the player has to build a city. The bigger the city you build, the more points you can receive. To accomplish this, you have to combine elements (*e.g.* trees and houses) in a strategical way. Moreover, you have to block bears that try to hinder you in building the city. In this way, the child learns to think strategically in order to overcome challenges. Moreover, children learn to keep a goal and to persevere in order to reach this goal. However, the game is not specifically focused at reducing anxiety levels, which makes ‘Triple Town’ a suitable game for the control condition.

The gaming sessions will be led by qualified therapists, or by master students who are supervised by qualified therapists. In session 1, the therapist starts with psycho-education on anxiety. After that, the anxiety of the child will be discussed, the therapist will explain the game and eventually the therapist will clarify that this game is focused on decreasing the anxiety of the child. Then, the child will play the game for approximately 40 min. After playing the game, the therapist will ask the following standardized questions: 1) How did the gaming go today? 2) What did you find difficult/What did you find easy? 3) What did you learn in the game? 4) Could you apply and practice the skills you have learned in scary or difficult situations in daily life? In session 2–6, the therapist will start the session with discussing the previous week and the skills the child has practiced at home. When the child mentions that he has practiced the skills in a scary or difficult situation, this will be reinforced by the therapist. In this way, the therapist does not add explicit therapeutic elements to the gaming sessions, but children do get stimulated to think about their anxiety and the way they can apply and practice the skills they have learned in the game in daily life.

### Study outcome measures

Table 1 shows an overview of the different time points, the questionnaires that were filled in on each time point and the informants that were involved.

**Table 1 Tab1:** Overview of assessments

	Screening	T0	T1	T2
Child				
Anxiety (SCAS-C)	χ	χ	χ	χ
Depression (CDI 2)		χ	χ	χ
Therapeutic expectancies (PETS)		χ		
Parent*				
Anxiety (SCAS-P)	χ	χ	χ	χ
Anxiety disorders (ADIS-P)		χ		χ
Depression (CDI 2:P)		χ	χ	χ
Social functioning (VISK)		χ	χ	χ
Behavior problems (SDQ)		χ	χ	χ
Therapeutic expectancies (PETS)		χ		
Teacher				
Social functioning (VISK)		χ	χ	χ
Behavior problems (SDQ)		χ	χ	χ

*The primary caregiver of the child will fill in the questionnaires. The ADIS-P will be conducted with both parents (if possible)

### Screening measures

To test their eligibility, children will be screened on anxiety symptoms using the SCAS-C for child report and the SCAS-P for parent report [28, 29]. Children are eligible for participation when the child and/or the parent report the presence of subclinical child anxiety. Moreover, demographical questions (*e.g.* sex, age, educational level) will be asked to both children and parents. Finally, some questions about the child’s gaming behavior (*e.g.* ‘How many hours per week do you game?’) will be asked.

### Primary outcome measure

*Anxiety symptoms* will be measured with the Dutch translation of the Spence Children’s Anxiety Scale (SCAS; [28]). The SCAS consists of 44 items (*e.g.* ‘I am afraid when I have to sleep alone’, ‘I worry about things’) on a 4-point scale, ranging from ‘never’ to ‘always’. Scores on items ranged from 0 to 3, with higher scores indicating more anxiety symptoms. Moreover, the scale consists of six subscales that are in line with the different anxiety disorders that are described in the DSM-IV: panic/agora phobia, separation anxiety, social phobia, generalized anxiety, obsessive compulsive anxiety and anxiety for physical injury. The SCAS has a high validity and reliability [36, 37].

### Secondary outcome measures

*Anxiety of the child according to the parents* will be measured with the Dutch translation of the Spence Child Anxiety Scale for Parents (SCAS-P; [29]). The SCAS-P consists of 38 items on a 4-point scale ranging from 0 (never) to 3 (always). The items of the SCAS-P were formulated as closely as possible to the corresponding item of the child version of the SCAS. Only items referring to an internal state (*e.g.* item 4: ‘I feel afraid’) were rephrased into observable behaviour for parents (*e.g.* ‘My child complains of feeling afraid’). The SCAS-P consists of the same six subscales as the child version. The SCAS-P has a good reliability and validity [38].

*The presence of anxiety disorders according to the parents* will be assessed with the Dutch translation of the Anxiety Disorders Interview Schedule for DSM-IV, Parent version (ADIS-P; [27]). This is a semi-structured diagnostic parent interview that can be used to diagnose anxiety disorders in children of 7–17 years old. The interview will be administered by a qualified therapist or by a master student under supervision of a qualified therapist. In this study, the presence of the following DSM-IV anxiety disorders will be examined: separation anxiety disorder, social phobia, specific phobia, panic disorder, agora phobia and generalised anxiety disorder. The interview consists of standardized questions, with ‘yes’, ‘no’ and ‘different’ as possible answers. At the end of the interview, the interviewer has to give his/her clinical judgement about the severity of every disorder. On basis of this judgement, the interviewer will make a definitive decision about the presence (yes/no) of the different anxiety disorders. The ADIS-P has a strong reliability and validity [27].

*Depressive symptoms* will be measured using the Dutch translation of the Child Depression Inventory 2 (CDI 2; [39]). The CDI 2 consists of 28 items measured on a 3-point scale ranging from 0 (depressive symptom is absent) to 2 (depressive symptom is always present) (*e.g.*, ‘I don’t feel alone’ = 0, ‘I often feel alone’ = 1, ‘I always feel alone’ = 2; ‘Sometimes I’m sad’ = 0, ‘I’m often sad’ = 1, ‘I’m always sad’ = 2). The children have to choose the answer that is most in accordance with their own thoughts and feelings. The validity and reliability of the Dutch CDI 2 (:P) is still being investigated, but it already has been shown that the original (American) version of the CDI 2 (:P) [40] has a good reliability, internal consistency and convergent validity [41].

*Depression according to the parents* will be measured with the Dutch translation of the Child Depression Inventory 2 for parents (CDI 2:P; [39]) will be used to measure parental assessment of depressive symptoms of their child. The CDI 2:P consists of 17 items measured on a 4-point scale ranging from 0 (not at all), 1 (some of the time), 2 (often), or 3 (most of the time) (*e.g.* ‘My child looks sad’; ‘My child seems lonely’). The parent has to assess to which extent the items are in accordance with their child’s thoughts and feelings.

*Social functioning according to the parents and teacher* will be measured with the ‘Vragenlijst voor Inventarisatie van Sociaal gedrag van Kinderen’ (VISK), a Dutch translation of the Children’s Social Behaviour Questionnaire (CSBQ; Luteijn [42]). The VISK consists of 49 items measured on a 3-point scale (0 = not applicable, 1 = sometimes applicable, 2 = often applicable). The items are divided over six problem scales: being not well tailored to social situations; limited tendency to engage in social interactions; orientation problems in time, space and place; not understanding social information; stereotype behavior; and anxiety for and resistance against changes. Hartman and colleagues [43] reported that the VISK has a good validity and reliability.

*Internalizing and externalizing behaviour problems according to the parents and teacher* will be measured with the Dutch translation of the Strengths and Difficulties Questionnaire (SDQ; [44]). The SDQ consists of 25 items, measured on a 3-point scale (0 = not true, 1 = a little bit true, 2 = certainly true). Moreover, an impact supplement can be completed, by which the impact of the behavior problems on daily functioning of the child and its family can be assessed. The items of the SDQ are divided over the following scales: emotional problems, behavior problems, hyperactivity/ attention problems, problems with peers and social behavior. There are separate forms for parents and teachers. The SDQ has a sufficient reliability and validity [45].

*Treatment expectancies according to child and parents* will be measured using the Dutch translation of the Parent Expectancies for Therapy Scale (PETS; [46]). The PETS has a parent and child version, and each version consists of seven items measured on a 6-point scale ranging from 1 (I totally disagree) to 6 (I totally agree). The items of the PETS are divided over the following subscales: credibility, child improvement and parent involvement. The PETS has a good validity and reliability [47].

### Data analysis/statistical analysis

Following the intention-to-treat principle [48], all children randomized to a condition will be included in the analyses to test the study objectives. Multiple imputations will be used for missing observations at post-intervention and 3-month follow-up. Reporting of the results of the study will be in accordance with the CONSORT 2010 Statement [25].

To investigate the differences in the development of anxiety symptoms between children in the experimental condition and children in the control condition, a 3 (within-subjects: pre, post, follow-up) by 2 (condition: experimental vs. control) ANOVA (repeated measures) will be conducted, with anxiety symptoms (child report) as the dependent variable. The direct effect of Mindlight on parent report of child anxiety, parent/child report of depressive symptoms, and parent/teacher report of social functioning and behavior problems will be investigated in the same way. Furthermore, remission rates of the anxiety disorders that were diagnosed at baseline (with ADIS-P) will be calculated at 3-months follow-up, and Chi-square (*χ*^2^) tests will be conducted to compare remission rates between the experimental and control group. In the above mentioned analysis plan it is assumed that the children will play the game individually and that therefore the data will not be clustered. However, in case of clustered data due to the formation of groups in which several children play the game in the same room, the analyses will be conducted in MPLUS 6.11 [49].

Finally, possible baseline differences between the two conditions in demographic variables (*e.g.* age, sex, educational level), anxiety symptoms, gaming behaviour and treatment expectancies will be checked. Moreover, possible differences in TAU between the experimental and control condition will be checked at all time points. Variables that show different distributions between the two groups will be entered as confounders in all models testing the effectiveness of the intervention.

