**Discussion:**

This paper aims to describe a study that will examine the effect of the serious game Mindlight on (sub) clinical anxiety symptoms of children with an ASD in the age of 8–16 years old. It is expected that children in the experimental condition will show lower levels of anxiety symptoms at 3-months follow-up, compared to children in the control condition. If Mindlight turns out to be effective, it could be an important contribution to the already existing interventions for anxiety in children with an ASD. Mindlight could then be implemented as an evidence-based treatment for anxiety symptoms in children with an ASD in mental health institutes and special education schools.

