### Sample size

A priori power analysis was performed in G*Power 3.1 [30] to calculate the sample size that is required in the present study. It is expected that Mindlight is significantly more effective in reducing anxiety symptoms of the participating children than Triple Town. Previous studies on the effect of already existing modified versions of CBT on anxiety among children with an ASD reported moderate to large effect sizes on anxiety symptoms (*e.g.* [31, 12, 32]). It is assumed that the implementation of Mindlight in clinical practice is worth consideration, when the effect of Mindlight is at least equal to the effect of the present anxiety treatments for children with an ASD. Therefore, the power calculation is conducted with a moderate expected effect size (f = .25) of condition (experimental or control condition) at 3-months follow-up. Moreover, it was expected that the Type I error was .05 and that the Type II error was .20 (power is .80). When computing these assumptions, it was calculated that a sample of 86 participants would be satisfactory in the present study. Eventually, the sample size was increased by 40 % to compensate for loss to follow-up (estimated at 20 %) and possible loss of power due to potential clustering of data in case of group formation (estimated at 20 %), resulting in 120 participants (60 in experimental condition and 60 in control condition).

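### The primary 3x2 repeated-measures ANOVA treats baseline as an outcome level and names no contrast at 3-months follow-up, where the expected effect and the power calculation sit

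*Protocol article*

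**What the plan says.** The abstract's Discussion states the expected result at one time point: "It is expected that children in the experimental condition will show lower levels of anxiety symptoms at 3-months follow-up". The Conclusion repeats it. The Sample size section uses "a moderate expected effect size (f = .25) of condition (experimental or control condition) at 3-months follow-up", and after setting alpha .05 and power .80 concludes that "a sample of 86 participants would be satisfactory in the present study". This is raised to 120, partly for an estimated 20% loss to follow-up.

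The Data analysis section fixes the primary model for child-reported anxiety: "a 3 (within-subjects: pre, post, follow-up) by 2 (condition: experimental vs. control) ANOVA (repeated measures) will be conducted". Its declared purpose is to compare how anxiety develops in the two conditions. It does not say whether the main effect or the interaction decides, and it names no comparison at follow-up. The continuous secondary outcomes are to be analysed in the same way. For missing data, "Multiple imputations will be used for missing observations at post-intervention and 3-month follow-up". Baseline anxiety is among the variables checked for imbalance, and any variable found to differ is then entered as a confounder in all effectiveness models.

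**The concern.** The expectation and the effect size are about a difference at T2, and the planned model has no term that equals that difference. The condition main effect averages T0, T1 and T2, although no treatment has been given at T0. The condition-by-time interaction asks whether the between-group difference varies anywhere over the three times, so it can be significant because of T1 alone.

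Baseline SCAS-C is used as an outcome level, not as a predictor of T2. If it happens to differ between the arms, the plan would also enter it as a covariate, so it would be both outcome and covariate in one model.

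At stake are a positive omnibus result that does not show a benefit at three months, a real three-month benefit that is missed, and a choice between main effect and interaction that stays open until results are seen.

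**Working it through.** **Inputs from the protocol article.** f = .25 at T2, which is d = 2f = .5 for two equal groups; alpha .05; target power .80; N = 86 before inflation; 120 randomised 1:1; 20% loss, so 120 × .8 = 96 evaluable at T2.

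**Assumptions not in the document.** SD 1, equal correlation ρ between time points, and the profile of the between-group difference over T0/T1/T2. The 96 is taken as the effective number, since imputing a missing T2 score does not restore the lost information.

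**1. The plan's own figure.** For the G*Power between-factors test in a repeated-measures ANOVA with m = 3 measurements, λ = f²·N·m / (1 + (m − 1)ρ), with 1 and N − 2 df. At ρ = .5 and N = 86, λ = .0625 × 86 × 3 / 2 = 8.06 and power is .801; at N = 84 it is .792. So 86 is reproduced as a main effect over three time points with ρ = .5. An unadjusted two-group comparison at T2 alone needs 128 (λ = .0625 × 128 = 8.0). The 120 follows from 86 × 1.4 = 120.4.

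**2. Three candidate tests.** Let δ be the difference at each time and δ̄ its mean over the three times.
- Main effect: λ = (N/4)·δ̄²·3 / (1 + 2ρ), df 1 and N − 2.
- Interaction: λ = (N/4)·Σ(δ − δ̄)² / (1 − ρ), df 2 and 2(N − 2).
- Baseline-adjusted T2 contrast (ANCOVA): λ = (N/4)·d² / (1 − ρ²), df 1 and N − 3.

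With N = 96 and ρ = .5:
- ANCOVA: 24 × .25 / .75 = 8.0, power .80.
- Sustained effect (0, .5, .5): interaction 24 × .1667 / .5 = 8.0, power .71; main effect 24 × .1111 × 3 / 2 = 4.0, power .51.
- Growing effect (0, .25, .5): interaction 24 × .125 / .5 = 6.0, power .58; main effect 24 × .0625 × 3 / 2 = 2.25, power .32.

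Simulation with 4000 runs per setting agreed at ρ = .5: ANCOVA .80, interaction .71 and .58, main effect .52 and .32.

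**3. Can the interaction tell T1 from T2?** For a T1-only effect (0, .5, 0), Σ(δ − δ̄)² is .1667, the same as for (0, .5, .5). Power is therefore identical: .71 at ρ = .5 (.56 at ρ = .3, .91 at ρ = .7).

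**4. Sensitivity, N = 96, d = .5 at T2.** Paired values are sustained / growing.

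| ρ | ANCOVA at T2 | Interaction | Main effect |
|---|---|---|---|
| .3 | .72 | .56 / .44 | .60 / .38 |
| .5 | .80 | .71 / .58 | .51 / .32 |
| .6 | .86 | .81 / .68 | .47 / .29 |
| .7 | .92 | .91 / .81 | .44 / .27 |
| .8 | .98 | .98 / .94 | .41 / .26 |

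With serial correlation (.7 adjacent, .49 between T0 and T2) and a sustained effect, the interaction has .81 and ANCOVA .80. For a fading effect (0, .75, .5) the interaction is ahead: .92 against .80 at ρ = .5, and .99 against .92 at ρ = .7.

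**5. Size for the T2 contrast.** At ρ = .5, 80% power needs 98 evaluable children. With 96 power is .80 (.799), and with an effective 86 it is .75.

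**The case against.** The 3x2 ANOVA is conventional and, under randomisation, its interaction is a valid test of differential change. The section's declared purpose points to the interaction, so the low main-effect figures may describe a test that nobody intends to use. The primary aim and the primary outcome name no time point, and the Design section evaluates the effect at both T1 and T2, so a T1 benefit is within the aim. Follow-up contrasts, sphericity corrections and pooling over imputations are commonly left to a full analysis plan, which is not shown.

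Much of this stands. A reader might infer that the T2 contrast is clearly more powerful in general. The documents do not support that, because they give neither the correlation nor the effect profile, and some plausible combinations show no gain or a loss against the interaction. A reader might also infer that the trial will contain no test at T2. The text supports only that none is named. Sphericity and pooling are not counted here.

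What does not fall is the mismatch within the article. It fixes an omnibus model while placing its expectation and effect size at T2. Where the effect is larger at T1 and the interaction has more power, a significant omnibus result still does not show a T2 difference.

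**Conclusion.** The point holds as one about targeting, with a gain in power that depends on conditions. The primary analysis as written does not identify a test of the stated three-month expectation, and its interaction cannot separate a T1-only effect from a sustained one.

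At ρ = .5, 96 evaluable children and d = .5 at T2, the baseline-adjusted T2 contrast gains 9 points over the interaction for a sustained effect and 22 for a growing one. At ρ = .7 the gain is about 1 to 12 points. At ρ = .8 it is nil for a sustained effect, and it turns negative for a fading one. Against the main effect, the test that reproduces 86, the gain is about 12 to 72 points over ρ = .3 to .8 for sustained or growing effects. All of this rests on compound symmetry. The choice ρ = .5 is inferred only from its reproducing 86.

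It would be too strong to call the ANOVA invalid, or to say that a T1 benefit would be a false finding. The stated aim is not tied to T2 consistently enough for that.

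**What to change.** State one primary test: the condition difference in SCAS-C at T2 with its 95% CI, adjusted for baseline SCAS-C in every case and not only when an imbalance is seen. Either ANCOVA on the imputed data or a mixed model for T1 and T2 with baseline SCAS-C as covariate will serve. Make the T1 difference secondary, and use the same form for the continuous secondary outcomes. SCAS-C is already collected at T0, T1 and T2, so no new data are needed.

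There are two costs. A T1-only effect, or the excess of a larger T1 effect, no longer counts towards the primary result. The Sample size section must also be restated for this test, with its assumed correlation: at ρ = .5, power is about .80 with 96 evaluable children. It is .75 at an effective 86, which matters because the 120 also includes a separate 20% allowance for clustering. The fallback to MPLUS for clustered data should be worded for the same contrast. The change should be made before the data are analysed.

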### Design

The present study involves a randomized controlled trial (RCT) with two conditions (experimental versus control), in which it is investigated whether the new video game Mindlight is effective in treating (sub) clinical anxiety symptoms in children with an ASD. For this study, children in the age of 8–16 years old with a diagnosis of an ASD according to the Diagnostic and Statistical Manual of Mental Disorders 4th Edition – Text Revision (DSM-IV-TR; [26]) will be screened for anxiety symptoms. The children with (sub) clinical anxiety symptoms will be selected and approached for participation.

After the selection and recruitment, children will be randomly assigned to the experimental or control condition. At baseline (T0), children, parents and teachers will fill in questionnaires. Moreover, parents will undergo a semi-structured interview (ADIS-P; [27]) to determine whether their child meets the criteria of one or more anxiety disorders. At post-intervention (T1) and at 3-months follow-up (T2), children, parents and teachers will fill in questionnaires again to evaluate the effect of Mindlight. At 3-months follow-up, parents will undergo the semi-structured interview again to test whether Mindlight also had an effect on the present anxiety disorder (s) in the participating children. Fig. 1 shows a schematic overview of the design in the present study.

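### The ADIS-P remission comparison does not make the child the unit of analysis, and its chi-square test cannot carry the confounders the plan promises

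*Protocol article*

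**What the plan says.** In the protocol article, Data analysis/statistical analysis, "remission rates of the anxiety disorders that were diagnosed at baseline (with ADIS-P) will be calculated at 3-months follow-up", and chi-square "tests will be conducted to compare remission rates between the experimental and control group". Missing follow-up observations are to be multiply imputed. Variables distributed differently between the arms are to enter every model of effectiveness as confounders.

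The Design section gives the purpose of the two ADIS-P interviews. The baseline interview (T0) is "to determine whether their child meets the criteria of one or more anxiety disorders". The 3-month interview (T2) is "to test whether Mindlight also had an effect on the present anxiety disorder (s) in the participating children".

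Secondary outcome measures lists what is rated: "separation anxiety disorder, social phobia, specific phobia, panic disorder, agora phobia and generalised anxiety disorder". It leaves the diagnosis to the rater: "On basis of this judgement, the interviewer will make a definitive decision about the presence (yes/no) of the different anxiety disorders". On staffing it says: "The interview will be administered by a qualified therapist or by a master student under supervision of a qualified therapist". The Intervention section describes the session leaders in the same terms: "The gaming sessions will be led by qualified therapists, or by master students who are supervised by qualified therapists".

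**The concern.** Three features of the stated analysis cause difficulty.

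- **Unit.** The rate is attached to disorders, a child can have more than one, and no sentence makes the child the unit. A chi-square test assumes independent observations. Two disorders in the same child, rated in one interview by one person, are unlikely to remit independently.
- **Covariates.** A plain chi-square test takes none, so the remission comparison cannot follow the adjustment rule in the same section.
- **New disorders.** Only T0 diagnoses are followed. A child who loses one disorder and acquires another by T2 could be counted as a success, although the T2 interview would have recorded the new disorder.

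A fourth issue concerns the rating. Presence of a disorder rests on the interviewer's judgement, interviewers and session leaders come from the same staff groups, and the article states no rule that keeps the two roles apart for a given child.

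At stake is the only diagnostic outcome in the trial. A p-value that is too small, or a rating made by someone who knows the game played, would weaken any statement that Mindlight affects anxiety disorders.

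**Working it through.** **The plan's own figures.** No sample size or power is given for remission. The stated sample size is for anxiety symptoms: f = 0.25, alpha 0.05, power 0.80, 86 children, raised by 40% to 120. It reproduces as the between-group effect in a repeated-measures ANOVA with m = 3 measurements and correlation 0.5 (the correlation is assumed):

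- λ = f²·N·m / (1 + (m − 1)·ρ) = 0.0625 × 86 × 3 / 2 = 8.06, which gives power 0.801.
- 86 × 1.4 = 120.4, stated as 120.

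Nothing below affects these figures.

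**Inputs for remission.** From the article: six disorders, one or more possible per child, 120 randomised (60 per arm). Assumed, because the article gives no value: mean number of disorders per diagnosed child k (1.5 to 3) and within-child correlation of remission, ICC (0.1 to 0.8).

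**Reading A: all T0 disorders pooled in one table.** The variance is inflated by DE = 1 + (k − 1)·ICC. The true type I error of a nominal 5% test is 2·[1 − Φ(1.96/√DE)]. For k = 2 and ICC = 0.5, DE = 1.5, 1.96/√1.5 = 1.60, and the error is 0.110. Over the range:

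| k | ICC 0.1 | ICC 0.3 | ICC 0.5 | ICC 0.8 |
|---|---|---|---|---|
| 1.5 | 0.056 | 0.068 | 0.080 | 0.098 |
| 2 | 0.062 | 0.086 | 0.110 | 0.144 |
| 3 | 0.074 | 0.121 | 0.166 | 0.224 |

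A beta-binomial simulation agrees. It used 20,000 runs, a remission probability of 0.4, children with 1, 2 or 3 disorders in shares 40%, 35% and 25%, and 24, 39 or 60 children per arm. Type I error ran from 0.063 (ICC 0.1) to 0.166 (ICC 0.8).

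**Reading B: one test per disorder.** Each child counts once within a test. With six independent tests at 5%, the chance of at least one false positive is 1 − 0.95⁶ = 0.265. Positive correlation between the tests would lower this.

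**Reading C: one remission flag per child, one test.** Type I error is the nominal 0.05. The article does not specify this reading, and even here the test carries no covariates.

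**New disorders.** Under Reading A, the lost disorder is a remission and the new one is outside the table. Under Reading C, if the flag looks only at T0 diagnoses, the child is remitted. Under either, the new disorder is not counted.

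**How many children enter.** A child without a T0 disorder cannot remit, and subclinical anxiety is enough for entry (Screening measures). The number with a T0 disorder is unknown. The Background cites about 40% of children with ASD as having a disorder and 21% as subclinical. Taking 40% as the low end and 40/(40 + 21) = 66% as the high end, both assumed:

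- 120 × 0.40 = 48 children, about 24 per arm.
- 120 × 40/61 = 79 children, about 39 per arm.

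Child-level power for 20% versus 40% remission (illustrative rates) is 0.32 at 24 per arm and 0.49 at 39. It would be 0.67 if all 60 per arm had a disorder.

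**The case against.** The strongest reply is that the article never says disorders will be pooled. It names no unit, the plural in its mention of tests fits one test per disorder, and a child-level flag is also compatible. A condensed article may leave the unit of a secondary test to the full plan. It follows that a reader may not infer that children will be counted several times, only that the wording allows it. The objection does not remove the point: of the three readings, only the one the article does not specify keeps 5% error, and none of them accommodates the promised confounders with the stated test.

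A reader might also infer that restricting to T0 disorders biases the denominator. The documents do not support that. Remission of T0 diagnoses is a usual endpoint and matches the purpose given in Design. T0 status is established before play, so the restriction makes the comparison smaller rather than demonstrably biased. Design does describe allocation before T0, which leaves open whether the T0 interviewer knows the arm, but nothing says so.

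Nor do the documents say that a child's own session leader does the interview. That possibility follows from matching staff descriptions and the absence of a separating rule, and assessor masking may be set out in the full protocol. What remains is a precaution.

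Finally, 66% is not the article's estimate of its case mix. It combines prevalences from two different cited studies and applies them to a sample recruited by questionnaire, partly from mental health institutes. It serves only as one end of a range.

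**Conclusion.** The point holds as a weakness in the definition and method of a secondary analysis. As worded, the comparison does not fix the child as the unit. The pooled reading gives a type I error of about 0.06 to 0.22 and the per-disorder reading a family-wise error of up to about 0.26. The first range rests wholly on assumed numbers of disorders and assumed correlations; the second is an upper figure under independence and matters only if any one of the six results would be taken as evidence. Two parts need no assumption: chi-square cannot carry the confounders required elsewhere in the same section, and disorders that first appear at T2 have no place in the stated comparison.

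The claims that remission will be double-counted, that its denominator is biased, or that session leaders will rate their own children go beyond the text.

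**What to change.** 1. Define one binary outcome per child: free of all six ADIS-P disorders at T2, among children with at least one at T0.
2. Analyse it with a single logistic regression on condition plus the covariates the plan carries in its other models, within the planned multiple imputation. Report a risk difference with 95% CI, obtained by averaging the model's predicted risks under each condition.
3. Show remission for each disorder descriptively, without tests.
4. As a supporting analysis, model the presence of any of the six disorders at T2 in all randomised children, adjusted for T0 status. This brings in children who entered with subclinical anxiety and counts new disorders. It mixes persistence with onset, so it should stand beside the remission result and not replace it.
5. Have each T2 interview done by an existing therapist or student who did not lead that child's sessions and is not told the condition.

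The cost is slightly more analysis work and a constraint on the interview rota. No new visits, instruments or participants are needed. With perhaps 48 to 79 children in the main remission analysis (assumed), the interval will be wide, and the report should say so.
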